# Induction of labour versus expectant monitoring for gestational hypertension or mild pre-eclampsia between 34 and 37 weeks' gestation (HYPITAT-II): a multicentre, open-label randomised controlled trial

**DOI:** 10.1186/1471-2393-11-50

**Published:** 2011-07-07

## Abstract

**Background:**

Gestational hypertension (GH) and pre-eclampsia (PE) can result in severe complications such as eclampsia, placental abruption, syndrome of Hemolysis, Elevated Liver enzymes and Low Platelets (HELLP) and ultimately even neonatal or maternal death. We recently showed that in women with GH or mild PE at term induction of labour reduces both high risk situations for mothers as well as the caesarean section rate. In view of this knowledge, one can raise the question whether women with severe hypertension, pre-eclampsia or deterioration chronic hypertension between 34 and 37 weeks of gestation should be delivered or monitored expectantly. Induction of labour might prevent maternal complications. However, induction of labour in late pre-term pregnancy might increase neonatal morbidity and mortality compared with delivery at term.

**Methods/Design:**

Pregnant women with severe gestational hypertension, mild pre-eclampsia or deteriorating chronic hypertension at a gestational age between 34^+0 ^and 36^+6 ^weeks will be asked to participate in a multi-centre randomised controlled trial. Women will be randomised to either induction of labour or expectant monitoring. In the expectant monitoring arm, women will be induced only when the maternal or fetal condition detoriates or at 37^+0 ^weeks of gestation. The primary outcome measure is a composite endpoint of maternal mortality, severe maternal complications (eclampsia, HELLP syndrome, pulmonary oedema and thromboembolic disease) and progression to severe pre-eclampsia. Secondary outcomes measures are respiratory distress syndrome (RDS), neonatal morbidity and mortality, caesarean section and vaginal instrumental delivery rates, maternal quality of life and costs. Analysis will be intention to treat. The power calculation is based on an expectant reduction of the maternal composite endpoint from 5% to 1% for an expected increase in neonatal RDS from 1% at 37 weeks to 10% at 34 weeks. This implies that 680 women have to be randomised.

**Discussion:**

This trial will provide insight as to whether in women with hypertensive disorders late pre-term, induction of labour is an effective treatment to prevent severe maternal complications without compromising the neonatal morbidity.

**Trial Registration:**

NTR1792 Clinical trial registration: http://www.trialregister.nl

## Background

Hypertensive disorders (including gestational hypertension (GH) and pre-eclampsia (PE)) complicate 10% of all pregnancies and can result in severe complications for the mother such as eclampsia, placental abruption, pre-term delivery, the syndrome of Hemolysis, Elevated Liver enzymes and Low Platelets (HELLP) and ultimately even neonatal and maternal death [1]. Hypertensive disorders in pregnancy are the largest cause of maternal mortality in the Netherlands [2,3]. Unfortunately, maternal mortality in the Netherlands has increased over the past decade, with pre-eclampsia remaining the number one cause of maternal death [4].

The majority of the cases of GH and PE declare itself after 32 weeks. As the origins of hypertensive disorders are probably related to faulty implantation of the placenta early in pregnancy, the only causal treatment of the disease is immediate delivery. Delivery will result in removal of the placenta, which will result in disappearance of the signs and symptoms of GH or PE within a few days. The timing of induction of labour has been debated, as induction was thought to increase the number of caesarean sections and in case of pre-term delivery, might compromise neonatal outcome. Our recent HYPITAT-I study provided us evidence that in women with GH and PE above a gestational age of 37 weeks, induction of labour not only resulted in a decrease of progression to severe pre-eclampsia or maternal complications, but unexpected also in a decrease in the number of caesarean sections (19% versus 14%, RR 0.75, 95% CI 0.55 - 1.04) [5]. Moreover, induction of labour showed a trend to a better neonatal outcome, a better maternal quality of life and a reduction in costs [6,7]. However for women with GH, PE or deteriorating chronic hypertension in the late pre-term period (e.g. 34, 35 and 36 weeks' gestation), there remains uncertainty on the best policy. The situation in these patients is different, as apart from maternal morbidity, the condition of the child is at state. Late pre-term born children experience significantly more morbidity, compared to children born at term. Unfortunately, children born from mothers with a hypertensive disorder were mostly excluded from studies [8-10]. Thus, for women with hypertensive related complications of pregnancy between 34 and 37 weeks, the issue on whether these women should be monitored expectantly or not, remains an obstetric dilemma. In addition, the NICE guideline "hypertensive disorders during pregnancy" refers in the consensus statement to the issue of mild or moderate pre-eclampsia between 34 and 36 weeks of gestation in terms of a "grey zone" at which the optimal timing of birth is not clear and more research is necessary for this period [11].

In view of the relatively poor outcome of women with hypertensive pregnancy complications in The Netherlands as compared to abroad and in view of the neonatal morbidity in case of a late pre-term birth, there is a need for critical evaluation of the management of hypertensive diseases during pregnancy in the late pre-term period in the Netherlands.

With lack of good clinical evidence on the subject and the resulting practice variation, we think that additional data comparing immediate delivery and expectant monitoring in patients with hypertensive disease late pre-term are urgently needed. We therefore propose a nationwide randomised clinical trial and an economic cost analysis as well as quality of life analysis on the subject. We aim to provide data on the balance between cost (both financial and in terms of neonatal morbidity) and effects (prevention of maternal complications).

## Methods/design

### Aims

The aim of this study is to investigate whether planned induction of labour compared to expectant monitoring in women with gestational hypertension, mild pre-eclampsia or deteriorating chronic hypertension at gestational age of 34 - 37 weeks of pregnancy, will reduce maternal morbidity and/or increase neonatal morbidity. We hypothesize that induction of labour will reduce maternal morbidity and mortality, but to the costs of increased neonatal morbidity. The study will also provide insight on whether induction of labour in women with GH, PE or deteriorating chronic hypertension in the late pre-term period will influence the quality of life and costs compared to expectant monitoring. Long term follow-up of the neonates and the mothers will be formulated.

### Participant/Eligibility Criteria

Patients 18 years of age or older are eligible if they have gestational hypertension, mild pre-eclampsia or deteriorating chronic hypertension at a gestational age between 34^+0 ^and 36^+6 ^weeks of pregnancy. The diagnosis of GH is made in case the diastolic blood pressure is equal to or above 100 mmHg at two occasions at least six hours apart in a woman who was normotensive until at least 20 weeks of gestation. The diagnosis of mild PE is made in case the diastolic blood pressure is above 90 mmHg at two occasions at least six hours apart in a woman who was normotensive until at least 20 weeks of gestation and if proteinuria exists (> 300 mg total protein in a 24 hour urine collection or > 30 in a spot urine protein:creatinine ratio). The diagnose of chronic hypertension is made in case the diastolic blood pressure is equal to or above 90 mmHg at two occasions at least six hours apart, diagnosed before 20 weeks of gestation. Women with chronic hypertension are eligible in case there is need for additional medication or in case superimposed PE is diagnosed between 34^+0 ^and 36^+6 ^weeks' gestation.

Patients with singleton or multiple pregnancies are eligible, independent of the position of the fetus (i.e. cephalic or breech). Neither diabetes mellitus, nor small for gestational age nor a history of caesarean section are exclusion criteria. Randomisation only occurs after informed consent.

Exclusion criteria are a diastolic blood pressure equal to/greater than 110 mmHg despite medication, systolic blood pressure equal to/greater than 170 mmHg despite medication, proteinuria equal to/greater than 5 g/L, eclampsia, HELLP syndrome, pulmonary oedema or cyanosis, oliguria less than 500 ml in 24 hours, renal disease, heart disease, HIV-positive, non-reassuring fetal heart rate, zero-flow or reverse flow in the umbilical artery, fetal abnormalities including abnormal karyotype, severe pre-eclamptic complaints such as frontal headache or ruptured membranes.

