### Procedures, recruitment, randomisation and collection of baseline data

Eligible women will be identified by the local research coordinator and/or the staff of participating hospitals. After counselling and reading the patient information form, patients will be asked for written consent. We will provide patient information in Dutch as well as several other languages (Turkish, French, Spanish and English), in order to facilitate inclusion of patients from cultural minorities. After informed consent, patient data will be entered in a web-based database, which will also facilitate randomisation.

Prior to randomisation, we will perform a digital examination to establish a Bishop score and we will measure cervical length. Women will be randomly allocated to either delivery within 24 hours (experimental arm) or expectant monitoring (control arm) until 37 weeks of gestational age. The study will be an open label study, as it is impossible to blind the health care workers and patients involved for the strategy to which the woman is allocated. Randomisation will be performed centrally with the use of a permuted-block design, stratified for recruiting centre. Randomisation will be 1:1 for intervention and expectant monitoring management. Although it will not be possible to prevent all cross-overs, both strategies will be performed according to strict criteria, as mentioned below.

At study entry baseline demographic, past obstetric and medical history will be recorded into the web-based Case Report Form (CRF) that is accessible through a closed part of a central website. Details of delivery, maternal and neonatal assessments during pregnancy or post-partum are recorded in the CRF. The collected data will be coded and processed with adequate precautions to ensure patient confidentially.

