### Outcome measures

#### Primary outcome measure

The primary outcome measure will be a composite endpoint of maternal mortality, maternal complications (eclampsia, HELLP syndrome, pulmonary oedema, thromoembolic disease) and progression to severe pre-eclampsia. Eclampsia is defined as severe gestational hypertension or pre-eclampsia resulting in maternal seizures [14]. HELLP syndrome is defined as a complication of severe pre-eclampsia involving Hemolysis, Elevated Liver functions, and Low Platelets [14,15]. Thromboembolic disease is defined as deep-vein thrombosis, pulmonary embolism or both. Patients will be examined for deep-vein thrombosis by duplex Doppler if thrombosis is suspected from clinical examination. A diagnosis of pulmonary embolism will be confirmed by pulmonary angiography, computed tomography, magnetic resonance imaging or a ventilation-perfusion lung scan [16-18].

Progression to severe pre-eclampsia is defined as diastolic blood pressure equal/greater than 110 mmHg despite medication, systolic blood pressure equal/greater than 170 mmHg despite medication and/or proteinuria equal to/greater than 5 g/L.

The neonatal primary outcome will be respiratory distress syndrome (RDS). Diagnosis of RDS requires signs of respiratory distress, consistent radiologic features, and oxygen therapy with a fraction of inspired oxygen (FIO2) of 0.40 or greater for at least 24 hours or until death [19].

Secondary outcome measures

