### Statistical issues

#### Data analysis

Data will be analysed on an intention-to-treat basis. Analysis of data includes comparison of maternal baseline characteristics at randomisation, maternal morbidity and mortality until hospital discharge and 6 weeks post-partum, neonatal morbidity and mortality until hospital discharge, method of delivery, type of hospital care and days of maternal and neonatal hospital stay. Differences between groups with normally distributed data will be tested using the Student's *t *test and for data with a skewed distribution, a non-parametric Mann-Whitney U test will be used. Categorical data will be analysed with χ2 statistics. Calculation of the percentages will be based on the number of valid observations. Treatment effect will be presented as relative risk (RR) with 95% CIs, and where appropriate as absolute risk reduction with 95% CIs and number needed to treat. A p-value of less than 0.05 indicates statistically significance. To asses treatment effects between different categories of patients in the trial we will perform subgroup analysis: per gestational age of the fetus per week (34^+0 ^- 34^+6^, 35^+0 ^- 35^+6 ^and 36^+0 ^- 37^+0^), parity (women with versus women without a previous vaginal delivery), hypertensive related disease (gestational hypertension versus pre-eclampsia), the use of corticosteroids (administered prior to delivery versus no use), mode of delivery (vaginal delivery versus caesarean section), caesarean delivery in history (history of a caesarean delivery versus no history of caesarean delivery) and the Bishop score (< 2, 2-6 and > 6).

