#### Sample size

We hypothesize that immediate delivery can reduce maternal complications from 5% to 1%. Using a two sided test (alpha error 5%, beta error 20%) and assuming a 10% rate lost to follow-up and protocol violations, we aim to recruit 680 patients. This sample size is also large enough to assess whether there will be relevant differences in the primary neonatal outcome (incidence of RDS around 10% at 34 weeks versus 1-3% at 37 weeks).

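### Multiple pregnancies are eligible, but the plain chi-square and relative-risk interval state no unit for neonatal outcomes; counted per infant, they ignore clustering within mothers

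*Protocol article*

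**What the plan says.** All references are to the protocol article.

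- Participant/Eligibility Criteria: "Patients with singleton or multiple pregnancies are eligible". No expected share of multiples is given.
- Procedures, recruitment, randomisation and collection of baseline data: "Women will be randomly allocated to either delivery within 24 hours (experimental arm) or expectant monitoring (control arm"). The woman is the randomised unit, in a 1:1 ratio.
- Primary outcome measure: "The neonatal primary outcome will be respiratory distress syndrome (RDS"). It is diagnosed from respiratory signs, radiology and oxygen need, all observed in the infant.
- Secondary outcome measures: the neonatal list (for example hypoglycaemia, sepsis, low Apgar score, low cord pH, intensive care admission, death) consists of events in a child.
- Follow-up of women and infants: the two-year comparison is of how many children fall beyond a cut-off, and of mean scores.
- Data analysis: "Categorical data will be analysed with χ2 statistics", "Calculation of the percentages will be based on the number of valid observations", and "Treatment effect will be presented as relative risk (RR) with 95% CIs". Neonatal outcomes are not excepted, and no unit of analysis is named for them.

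No section mentions a clustered method, a per-pregnancy definition of a neonatal outcome, or a restriction to singletons.

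**The concern.** The ordinary chi-square and the usual interval for a relative risk assume independent observations. Co-twins share mother, allocation and essentially the same gestational age at birth, and usually the same antenatal corticosteroid exposure. The article itself ties RDS risk to gestational age (about 10% at 34 weeks against 1-3% at 37 weeks, Sample size section), so a positive correlation within pairs is plausible. Because both twins are in the same arm, that correlation adds to the variance of the difference between arms, and the named method does not count it.

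At stake is the precision of the neonatal side of the comparison. The trial weighs maternal benefit against neonatal morbidity and hopes to conclude on benefit without neonatal compromise. Intervals that are too narrow can mislead in two ways: they can declare a neonatal difference that is not there, or make an exclusion of harm look firmer than the data allow.

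**Working it through.** **The plan's own figure.** The Sample size section gives 680 women for a maternal composite falling from 5% to 1%, two-sided alpha 5%, power 80%, and 10% loss and protocol violations.

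- Pooled normal formula: 285 per arm, 570 in total, 570/0.9 = 633.3, so 634.
- With continuity correction: 333 per arm, 666 in total, 666/0.9 = 740.
- Two-sided Fisher exact test by enumeration: power 80.8% at 306 per arm, and 2 × 306/0.9 = 680.

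So 680 is reproduced with an exact test. It rests on one observation per woman, and twin clustering does not enter it.

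**Design effect for infant-level outcomes.** Let t be the share of women carrying twins and ρ the correlation of the outcome within a pair. An arm of n women has n(1 + t) infants. With risk p, the variance of the event count is

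p(1 − p)[n(1 − t) + 2nt(1 + ρ)] = n·p(1 − p)[1 + t + 2tρ].

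The chi-square uses n(1 + t)·p(1 − p). The ratio is

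DE = 1 + ρ·2t/(1 + t).

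The true two-sided alpha is 2[1 − Φ(1.96/√DE)], and the interval is too narrow by 1 − 1/√DE.

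**Inputs.** The article gives neither t nor ρ. Both are assumed here: t from 2% to 15%, ρ from 0.3 to 0.7, twins only.

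| t | ρ | DE | Interval too narrow by | True alpha |
|---|---|---|---|---|
| 2% | 0.3 | 1.012 | 0.6% | 5.1% |
| 2% | 0.7 | 1.027 | 1.3% | 5.3% |
| 5% | 0.3 | 1.029 | 1.4% | 5.3% |
| 5% | 0.7 | 1.067 | 3.2% | 5.8% |
| 10% | 0.3 | 1.055 | 2.6% | 5.6% |
| 10% | 0.7 | 1.127 | 5.8% | 6.5% |
| 15% | 0.3 | 1.078 | 3.7% | 5.9% |
| 15% | 0.7 | 1.183 | 8.0% | 7.15% |

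Worst case written out: 2 × 0.15/1.15 = 0.2609; DE = 1 + 0.7 × 0.2609 = 1.183; √DE = 1.0875; 1.96/1.0875 = 1.802; alpha = 7.15%, about 7.2%.

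**Check by simulation.** The ordinary chi-square was simulated with 306 women per arm and RDS at 5% in both arms. Without twins it rejected in 5.0-5.1% of runs. With ρ from 0.3 to 0.8 it rejected in 5.2-5.8% at 5% twins, 5.8-6.7% at 10%, and 6.5-8.1% at 20%. This agrees with the formula.

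**Power for RDS.** This takes the article's 10% and 3% as the two arm rates; they are quoted as rates by gestational age, so that is an assumption. With 306 women per arm, and infants n(1 + t) divided by DE, power is 93.6-95.4% over the table's range, against 94.6-96.6% if clustering is ignored. Widening to 20% twins and correlation up to 1 leaves it at about 92-97%.

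**The case against.** The strongest reply is that the error is conditional. The article nowhere says that co-twins will be treated as independent. The data analysis section names no unit for neonatal outcomes, and a chi-square on one observation per pregnancy would be valid. This stands, and it limits the claim: the unit is unstated, and the problem arises if the unit is the infant. The infant is still the natural reading, because the outcomes are defined by findings in a child and the two-year follow-up counts children.

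A second reply is that a journal article leaves such detail to the full protocol or analysis plan. Silence alone would not be a finding. But the article is not silent: it names one test for all categorical data without exception, and that test, followed as written on infants, gives wrong error bars for the population that the eligibility rule admits.

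A third reply is that the effect is small. This also stands. At 2% twins and correlation 0.3 the true alpha is about 5.1%, and the larger figures need a larger twin share and a high correlation. Randomisation is also stratified by centre. If RDS varies between centres, an analysis that ignores centre tends to be conservative, which is a partial offset of unknown size.

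The abstract lists RDS among secondary outcomes, while the outcome section calls it the primary neonatal outcome. Either way, the maternal composite is the endpoint on which the trial is sized.

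A reader might infer that the trial's sample size or main result is undermined. The documents do not support that: the maternal composite has one observation per woman. A reader might also infer that the only risk is false-positive neonatal differences. That is incomplete, since narrow intervals can equally exclude harm too readily.

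**Conclusion.** The point holds in conditional form and is of small to moderate size. Three features combine badly: eligible multiples, randomisation of the woman, and an unqualified chi-square with relative risk and 95% CI. Counted per infant, categorical neonatal outcomes then get standard errors that are too small under any positive correlation within pairs, and nothing in the article corrects this.

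The figures (design effect about 1.01-1.18, alpha about 5.1-7.2%, intervals about 1-8% too narrow) depend on the assumed twin share and correlation and on twins being the only multiples. The direction depends only on the infant being the unit and the correlation being positive.

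The chi-square does not govern every neonatal result. Neonatal hospital stay and the two-year mean scores fall under the t test or Mann-Whitney test, which assume independence too. The neonatal analysis should be corrected; the maternal analysis and the 680 need no change on this account.

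**What to change.** In the Data analysis section, state that the infant is the unit of analysis for neonatal outcomes. For categorical ones, replace the plain chi-square with a modified-Poisson or log-binomial GEE that takes the mother as the cluster, and report relative risk and risk difference with cluster-robust 95% CIs. Apply the same clustering to continuous neonatal and two-year outcomes.

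A per-pregnancy analysis (at least one child with RDS) is a different estimand: the risk that a pregnancy yields an affected child, not the risk per child. It belongs as a sensitivity analysis, not as an interchangeable alternative. A singleton-only analysis could be added in the same role.

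The change is one of wording and needs no further patients or data. Its cost is slightly wider intervals, by the amounts shown above under the assumed ranges.

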### Procedures, recruitment, randomisation and collection of baseline data

Eligible women will be identified by the local research coordinator and/or the staff of participating hospitals. After counselling and reading the patient information form, patients will be asked for written consent. We will provide patient information in Dutch as well as several other languages (Turkish, French, Spanish and English), in order to facilitate inclusion of patients from cultural minorities. After informed consent, patient data will be entered in a web-based database, which will also facilitate randomisation.

Prior to randomisation, we will perform a digital examination to establish a Bishop score and we will measure cervical length. Women will be randomly allocated to either delivery within 24 hours (experimental arm) or expectant monitoring (control arm) until 37 weeks of gestational age. The study will be an open label study, as it is impossible to blind the health care workers and patients involved for the strategy to which the woman is allocated. Randomisation will be performed centrally with the use of a permuted-block design, stratified for recruiting centre. Randomisation will be 1:1 for intervention and expectant monitoring management. Although it will not be possible to prevent all cross-overs, both strategies will be performed according to strict criteria, as mentioned below.

At study entry baseline demographic, past obstetric and medical history will be recorded into the web-based Case Report Form (CRF) that is accessible through a closed part of a central website. Details of delivery, maternal and neonatal assessments during pregnancy or post-partum are recorded in the CRF. The collected data will be coded and processed with adequate precautions to ensure patient confidentially.

A subset of 200 women will receive quality of life questionnaires prior to randomisation, one day after randomisation and subsequently after 1 week, 2 weeks, 6 weeks, 3 months and 6 months. Since the gestational age at delivery will differ between the two groups, we will ask the participating women also to complete questionnaires at 1 day and 2 days after delivery. A pain scale will be added to those questionnaires. We hypothesize differences on the emotional and anxiety scales prior to delivery and differences in physical scales after delivery (due to differences in instrumental delivery rates). The questionnaires will contain the Medical Outcome Study 36-Item Short Form Health Survey (SF-36), the European Quality of Life 6 dimensions 3 levels (EuroQoL 6D3L) with subsequent general health Visual Analogue Scale (VAS), the Hospital Anxiety and Depression scale (HADS), and the Symptom Check List (SCL-90), all validated in Dutch and English.

